## 8.3 Study procedures

### 8.3.1 Height – Standard care

Height will be measured in centimetre (cm). Height will be measured recumbent in centimetres in children unable to stand. Whenever the child can stand height will be measured using a stadiometer standing (without shoes) in centimetres (cm).

### 8.3.2 Weight – Standard care

Weight will be measured in kilograms (kg) in underwear without diaper.

### 8.3.3 Body Mass Index (BMI) – Standard care

BMI will be calculated by the following formula.  $BMI = \text{Weight (kg)} / \text{height (m)}^2$ . The Standard Deviation Score (SDS) of the Dutch growth standards will be calculated.

Overweight and obesity at the age of 2 year will be determined using the IOTF criteria. The participants will be compared to the Dutch population.

### **8.3.4 SCORAD Index – Extra in this study**

The SCORAD Index is a clinical tool used to assess the extent and severity of eczema. To determine extent, the sites of affected eczema are shaded on a drawing body. The affected area is calculated as a percentage of the whole body. In addition a representative area of eczema is selected. In this area the intensity of the signs redness, swelling, oozing/crusting, scratch marks, skin thickening (lichenification) and dryness each is assessed as none (0), mild (1), moderate (2) or severe (3). Subjective symptoms (i.e. itching, sleeplessness) are scored by the caregiver using a visual analogue scale. Zero means no itch/no sleeplessness and 10 is the worst imaginable itch (or sleeplessness). The SCORAD Index will be used during all the hospital visits; before the start of complementary feeding, at 1 and 2 years of age.

### **8.3.5 Health Related Quality of Life (HRQoL): Infant Toddler Quality of Life Questionnaire (ITQoL) or Pediatric Quality of Life Inventory (PedsQL) – Extra in this study**

HRQoL is a multidimensional concept covering different domains. These domains are physical, occupational, psychological and social functioning. Generic measures summarize a spectrum of domains and dimensions of health that apply equally and broadly to diverse conditions or populations. HRQoL in children will be measured using the Infant Toddler Quality of Life Questionnaire (ITQoL) or Pediatric Quality of Life Inventory (PedsQL).

The ITQoL was developed for use infants and toddlers from the age of 2 months to 5 years of age. This questionnaire has 97 items and measures 12 concepts and has to be completed by the parents. It is a generic HRQoL questionnaire. Per concept the items can be summed up and transformed into a 0 (worst possible score) to 100 (best possible score) scale. This questionnaire is used in different samples of Dutch children. The ITQoL is a generic HRQoL.

The PedsQL™ Measurement Model is a modular approach to measuring health-related quality of life (HRQOL) in healthy children and adolescents and those with acute and chronic health conditions. The PedsQL™ Measurement Model integrates seamlessly both generic core scales and disease-specific modules into one measurement system. The items of the four scales (Physical Functioning, Emotional Functioning, Social Functioning, and School Functioning) are grouped together on the actual questionnaire. Items are reversed scored and linearly transformed to a 0-

100 scale, so that higher scores indicate better HRQOL (Health-Related Quality of Life).

The parents will be asked to act as a proxy for their child and complete the questionnaire. The ITQoL or PedsQL will be measured at the age of 2 years. This questionnaire will be sent to the parents via Castor edc and will be filled out digitally.

### **8.3.6 Eating behavior – Extra in this study**

The Baby Eating Behaviour Questionnaire (BEBQ) will be measured before the start of complementary feeding (12 weeks or 17 weeks) in both preterm and term born children (control group B). This questionnaire will be sent to the parents via Castor edc and will be filled out digitally. The BEBQ is a parent-report measure of appetite during the milk-feeding phase of infancy. Four dimensions emerged, with 17 items tapping four distinct feeding traits and one item describing general appetite. 'Enjoyment of food' (4 items) related to the infant's perceived liking of milk and of feeding in general, 'food responsiveness' (6 items) evaluates how demanding the infant is with regard to being fed and his or her level of responsiveness to cues of milk and feeding, 'slowness in eating' (4 items) measures the speed with which an infant typically feeds, and 'satiety responsiveness' (3 items) assesses how easily the infant gets full during a feed. BEBQ has shown a good reliability, with a Cronbach's alpha between 0.73-0.81.

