1. Overweight (including obesity): to determine the effect of early versus late introduction of complementary feed on the BMI, according to the IOTF cut-off values at 1 year.
2. Eating behavior and tolerating complementary feeding: to determine if early introduction is correlated with less eating problems in comparison to introduction the late introduction, by using the Baby Eating Behaviour Questionnaire (BEBQ) and Child Feeding Questionnaire (CFQ).
  - a. Subgroup analysis will be performed to explore if children with respiratory problems after birth requiring intubation have more eating problems than children without respiratory problems requiring intubation
  - b. Subgroup analysis will be performed to study if the duration of a feeding tube after birth is correlated with eating problems
  - c. Subgroup analysis will be performed to study if gestational age is related to eating disorders.
3. Eating behavior and tolerating complementary feeding: to determine if term born infants (control group B) have less eating problems in comparison to preterm infants before the start of complementary feeding, by using the Baby Eating Behaviour Questionnaire (BEBQ)
4. Growth parameters (weight, length, head circumference, BMI, weight-for-age, length-for-age, head circumference-for-age): comparing the growth parameters of preterm infants with term infants before the start of complementary feeding, at 1 year and at 2 years
5. Taken into account the food diaries at 6 months, 9 months, 12 months and 24 months and the start of complementary feeding
6. Health Related Quality of life (HRQoL): to evaluate the difference in HRQoL between early versus late introduction of complementary feeding, by using The Infant Toddler Quality of Life (ITQoL) Questionnaire or Pediatric Quality of Life Inventory (PedsQL).
7. Ages and Stages Questionnaire (ASQ): to evaluate the difference in development between early versus late introduction of complementary feeding, by using the ASQ at the age of 1 and 2 years.
8. Allergy/Atopic: to evaluate if the incidence of allergies is different between early versus late introduction of complementary feeding, by using the SCORAD.
9. Microbiota: to evaluate if the microbiota change due to the introduction of complementary feeding

:

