##### **1. Hospital visit before the start of complementary feeding**

- a. Information about the randomisation will be given. Parents receive a letter in which is stated when to start with complementary feeding
- b. Weight, height, head circumference, and SCORAD score will be measured
- c. A diary regarding the breast- or formula milk is taken
- d. The Baby Eating Behavior Questionnaire is taken

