#### **Extra measurements:**

- SCORAD (**SCOR**ing**A**topic**D**ermatitis, a clinical tool used to assess the extent and severity of eczema).
- The eating behaviour (Baby Eating Behaviour Questionnaire (BEBQ)) is measured before the start of complementary feeding.
- Infant Toddler Quality of Life Questionnaire (ITQoL) or Pediatric Quality of Life Inventory (PedsQL) is measured at corrected age of 2 years.
- The Child Feeding Questionnaire (CFQ) will be measured at corrected age of 2 years.
- The Ages and Stages Questionnaire (ASQ) will be measured at corrected age of 1 and 2 years.
- Diary: Parents of all children are asked to complete three different diaries during the study period until age of 2 year.
  - Version 1 (Milk diary): A diary about the breast- or formula milk before the start of complementary feeding.
  - Version 2 (Start diary): A diary at the start of complementary feeding. Parents are asked to fill in when they give solid food for the first time, what kind of solid food they give and how much their child eats for the first time.
  - Version 3 (2 day diary): A 2-day diary method: Parents will be asked to fill in the food diary during two days, of which one day in the weekend. Parents are asked to do this at the age of 6 months, 9 months 1 year and 2 years.
- Microbiota: parents of all preterm children are asked to collect faeces at home at three different time points:
  - 10-11 weeks post term
  - 15-16 weeks post term

○ 20-21 weeks post term

If the parents give informed consent for collecting faeces, the preterm infants are part of group 2a. We will include a total of 150 patients for microbiota analysis. In case parents wish to attend the study without collecting faeces, they will be part of group 1 (see figure 1 and 2)

The measurements are collected at the hospital. If this is not possible, height and weight at the age of one and two years will be collected at the well baby clinics (with permission of the parents). The reach of the well baby clinics, part of the Child Health and Welfare service (JGZ), in the Netherlands is high. Ninety-eight percent of all the newborns and 95% of all the infants attend the well baby clinics. Regular visiting moments of the well baby clinics are given in table 2. The well baby clinics and the general practitioner will be informed about the study and the group in which the patients are allocated.

| Age                                  | Kind of contact        |

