#### 8.1.4 Study parameters tested in controls

The control group will be the group starting with complementary feeding at the corrected age of 17 weeks. All parameters will be tested in the intervention group and in the control group.

Control group B:

- Growth parameters: Length, weight and head circumference at 3 months (with an age range of 2 weeks), and 1 year and 2 years of age (with an age range of 6 weeks).
- Other parameters (see 8.1.3)
- BEBQ (questionnaire) at 10-12 weeks of age, supplemented with questions regarding the baby feeding
- Food diaries at 6 months, 9 months, 1 year and 2 years of age, supplemented with questions about the start of complementary feeding (retrospective)

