### **8.3.7 Child Feeding Questionnaire (CFQ) – Extra in this study**

The Child Feeding Questionnaire (CFQ) will be measured at the age of 2 years. This questionnaire will be sent to the parents via Castor edc and will be filled out digitally. It is a self-report measure to assess parental beliefs, attitudes, and practices regarding child feeding, with a focus on obesity proneness in children. The current version of the CFQ contains seven factors that fall into two categories. The first category, risk factors and concerns, measures factors that may elicit parental control in feeding and contains: perceived Feeding Responsibility, Perceived Parent Overweight, Perceived Child Overweight, and Concern about Child Overweight. The second category, control in child feeding: attitudes and practices, measures parents' attitudes and behaviors regarding child feeding and contains: Restriction, Pressure To Eat, and Monitoring. The reliability of both parents and child version is good: the Cronbach's alpha is respectively >0.70 and 0.66-0.88.

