## 10. STATISTICAL ANALYSIS

Since the sample size was not archived, the data will be interpreted with caution. Data will be analyzed on an intention to treat basis. In addition, we will also perform a per protocol analysis, taking into account the attrition rate. In case of missing values we will use multiple imputation. For the per protocol analysis, the criteria for the start of complementary feeding will be 12-13 weeks for the early group and 16-17 weeks for the late group. A p-value of 5% will be regarded as statistically significant and results will be presented with 95% confidence intervals.

Categorical data will be presented in absolute numbers and percentages. If a metric variable is normally distributed results will be shown in mean and standard deviation (sd). If a metric variable is not normally distributed median will be used with the interquartile range.

Descriptive data on BMI will be compared with the most recent Dutch growth chart. For the primary study parameter, the prevalence of obesity, the percentage of patients that develop overweight by using the IOTF will be calculated and intervention group and control will be compared including prevalence ratios with 95% confidence intervals. Furthermore, BMI and BMI z-scores between the intervention and control group will be compared as continuous variables.

The results of the questionnaires (BEBQ, CFQ, ITQoL / PedsQL, ASQ) will be analysed according to the scoring tables attached to the questionnaires. Allergy will be scored by a SCORAD form and can be presented as continuous or categorical variable. All blood and faeces results will be analysed as continuous or categorical variable. The diary results will be analysed as a continuous variable.

For all sub-objectives (as formulated in chapter 2), the intervention group and control group will be compared to determine the effect of early versus late introduction of complementary food, using a independent t-test or nonparametric test. For subgroup analysis, i.e. for children with respiratory problems or tube feeding, logistic regression will be used.

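### The between-arm part of sub-objective 2 has no valid child outcome: the BEBQ is taken before complementary feeding starts, and the CFQ measures the parents

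*Protocol*

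**What the plan says.** Sub-objective 2 (Protocol, Section 2) is "to determine if early introduction is correlated with less eating problems in comparison to introduction the late introduction". The only instruments it names are the BEBQ and the CFQ. Section 8.1.2 lists the child's eating behaviour and tolerance of complementary feeding as a secondary endpoint, using the same two instruments. Section 10 states that, for all sub-objectives, "the intervention group and control group will be compared to determine the effect of early versus late introduction of complementary food", with a t-test or nonparametric test.

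The BEBQ is scheduled in three places:

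- Section 3, first hospital visit, held before complementary feeding: "The Baby Eating Behavior Questionnaire is taken".
- Section 3, extra measurements: "The eating behaviour (Baby Eating Behaviour Questionnaire (BEBQ)) is measured before the start of complementary feeding".
- Section 8.3.6: "The Baby Eating Behaviour Questionnaire (BEBQ) will be measured before the start of complementary feeding (12 weeks or 17 weeks").

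The visit lists for 1 and 2 years contain no BEBQ. Section 8.3.6 describes it as a parent-reported measure of appetite while the infant is milk-fed.

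The CFQ is taken at 2 years. Section 8.3.7 says of it: "It is a self-report measure to assess parental beliefs, attitudes, and practices regarding child feeding".

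For term infants, Section 8.1.4 gives "BEBQ (questionnaire) at 10-12 weeks of age", while Section 3 (control group B) gives 3 months.

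**The concern.** The objective, endpoint, schedule and test are all stated in the protocol, and they do not fit together. One named instrument is completed before the exposure being compared. The other is completed afterwards but describes the parents. Neither can show whether an earlier start leaves the child with fewer eating problems or better tolerance of solids.

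A nominally significant BEBQ difference between arms could be published as an effect of timing, and a CFQ difference as evidence about the child's eating, when neither follows. No analysis method cures this. The mixed model in Section 10 needs repeated measurements, and the BEBQ has one time point.

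**Working it through.** **Question against instrument**

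| Instrument | When | What it records (protocol's description) | Can it show an effect of timing on the child's eating? |
|---|---|---|---|
| BEBQ | Once, before solids | Appetite in the milk phase: 4 + 6 + 4 + 3 = 17 items in four traits, plus one general appetite item | No: it precedes the exposure, and tolerance of solids cannot yet be seen |
| CFQ | 2 years | Seven factors: four on perceived responsibility, perceived weight and concern, three on control of feeding | No: all seven describe the parent's perceptions or practices |

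The protocol gets this right elsewhere. Section 8.3.9 takes stool samples at the same post-term ages in both arms: before either arm starts, after only the early arm has started, and after both have.

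**What a BEBQ difference between arms could mean**

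Randomisation makes the expected difference zero apart from two routes that do not involve feeding.

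1. Reporting. Allocation is open (Section 8.2), parents are told directly after randomisation (Section 5.5), and information on it is given at the visit where the BEBQ is taken (Section 3). Expectation could colour a parent-reported score.
2. Age. No common BEBQ age is fixed for the two preterm arms. If age at completion differs by arm, normal development could shift the score.

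With neither route at work, each 5% test rejects 5% of the time.

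**Illustration of the age route only**

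This matters only if ages differ by arm, which the protocol does not establish. It gives no BEBQ standard deviation or age trend, so the shift d (in SD units) is assumed. With n per arm, the two-sided 5% z-test rejects with probability

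1 − Φ(1.96 − d/√(2/n)) + Φ(−1.96 − d/√(2/n)).

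The planned arm size is 275 (Section 4.3). It was set for overweight, 6% versus 13%, and reproduces: (1.960·√(2·0.095·0.905) + 0.842·√(0.0564 + 0.1131))² / 0.07² = 274.3, rounded up to 275. Section 10 appears to say the target was not reached, so an assumed 150 per arm is shown too.

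| Assumed shift d | 150 per arm | 275 per arm |
|---|---|---|
| 0 | 5% | 5% |
| 0.1 SD | 14% | 22% |
| 0.2 SD | 41% | 65% |
| 0.3 SD | 74% | 94% |

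Example: n = 150, d = 0.2 gives √(2/150) = 0.1155 and 0.2/0.1155 = 1.73, so the rejection probability is 1 − Φ(0.23) = 41%.

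**Preterm-term comparison (sub-objective 3)**

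This comparison is meant to be made before solids, so the BEBQ suits it. What is loose is the age. Term infants are given as 10 to 12 weeks or as 3 months; the protocol treats 3 months as 12 weeks (Section 2) and as 13 weeks (Section 1.1.3), so the two statements differ by 0 to 3 weeks. The preterm age is not fixed.

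**The case against.** Several points on the other side have force.

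- **Ages by arm.** A reader might infer from Section 8.3.6 that the early arm is measured at 12 weeks and the late arm at 17, a gap of 5 weeks. The documents do not establish that. The bracket directly follows the mention of the start of complementary feeding and may only give the two start times. The same sentence covers term infants, who have no allocated start. Section 3 describes one pre-start visit for all preterm infants, and early-arm parents need their start letter before 12 weeks. What stands is that no common age is fixed.
- **All of sub-objective 2 lost.** A reader might conclude that nothing in it can be answered. That goes too far. Parts 2a to 2c (intubation, tube-feeding duration, gestational age) are not arm comparisons and can use a pre-start BEBQ.
- **Section 10 does not name the BEBQ in the arm comparison.** True: its sentence covers all sub-objectives, and read literally would include the preterm-term ones. Where Section 10 names a group comparison of the BEBQ, it is preterm versus term. That the arms will be compared on it is an inference, but a firm one, because sub-objective 2 and Section 8.1.2 both name it.
- **An overall false-positive rate.** One might count the BEBQ scales and compute the chance of at least one spurious finding. The protocol does not say which scores are tested, and the scales need not be independent, so no such figure is supported.
- **Other data exist.** The diaries record the first solid food, the amount eaten and later intake. They are not named as instruments for sub-objective 2. Section 8.3.7 gives reliability for a parent and a child version of the CFQ, but the questionnaire goes to parents and the listed factors are parental.

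**Conclusion.** The point stands for the early-versus-late comparison only. As planned, that part of sub-objective 2 and the matching secondary endpoint have no valid child outcome. The effect of timing on the BEBQ through feeding is zero by design, whatever the sample size, and the CFQ answers a different question. This follows from the protocol's own schedule and instrument descriptions and needs no outside figure.

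Its reach is limited to one secondary question; the primary endpoint is untouched. The rejection rates above 5% are conditional on an age difference between arms that the text allows but does not state, and on assumed shifts. The unfixed preterm age and the two term ages are a lesser matter to reconcile, relevant mainly to sub-objective 3.

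**What to change.** 1. Remove the BEBQ from the early-versus-late endpoints and tests in Section 2 (sub-objective 2), Section 8.1.2 and Section 10. Report it by arm as a baseline characteristic, without an effect claim.
2. Keep it for 2a to 2c and for sub-objective 3. Adjust the preterm-term comparison for age at completion (corrected age for preterm infants), and tabulate that age by group first. If the ranges barely overlap, say so, because adjustment would then be extrapolation.
3. Report the CFQ arm comparison as parental feeding practice, and draw no conclusion from it about the child's eating problems.
4. Reconcile Sections 3, 8.1.4 and 8.3.6 on when the BEBQ is completed.

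All four work on data already collected. The BEBQ is completed digitally, so completion dates should be retrievable (an assumption). The cost is rewording and one covariate.

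Optionally, and only if follow-up is still open, add a child eating-behaviour questionnaire at 2 years through the same digital system. That adds a small burden for parents and would give the between-arm question a child outcome. Otherwise the protocol should say that this question is not answered.

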### **8.3.7 Child Feeding Questionnaire (CFQ) – Extra in this study**

The Child Feeding Questionnaire (CFQ) will be measured at the age of 2 years. This questionnaire will be sent to the parents via Castor edc and will be filled out digitally. It is a self-report measure to assess parental beliefs, attitudes, and practices regarding child feeding, with a focus on obesity proneness in children. The current version of the CFQ contains seven factors that fall into two categories. The first category, risk factors and concerns, measures factors that may elicit parental control in feeding and contains: perceived Feeding Responsibility, Perceived Parent Overweight, Perceived Child Overweight, and Concern about Child Overweight. The second category, control in child feeding: attitudes and practices, measures parents' attitudes and behaviors regarding child feeding and contains: Restriction, Pressure To Eat, and Monitoring. The reliability of both parents and child version is good: the Cronbach's alpha is respectively >0.70 and 0.66-0.88.

### 8.3.8 Ages and Stages Questionnaire (ASQ) – Extra in this study

The Dutch version on the Ages and Stages Questionnaire extended version, third edition, (ASQ) will be measured at the age of 1 year and 2 years corrected age. This questionnaire will be sent to the parent digitally or will be filled in on paper. The ASQ is a validated parent-completed developmental screening tool that covers 5 developmental domains: communication, fine motor function, gross motor function, personal-social functioning, and problem solving. Each domain has 8 or 9 questions on developmental milestones. Parents evaluate whether the child has achieved a milestone (yes, 10 points), has partly achieved the milestone (sometimes, 5 points), or has not yet achieved the milestone (no, 0 points). ASQ total score is calculated by adding all the domain scores and dividing the total by 5. Parents will be sent the “extended ASQ version” so for 12 months the combined questions for 12 and 14 months and for 24 months the combined questions for 24 and 27 months to calculate both a score based on chronological age and a score corrected for prematurity to improve sensitivity. The time window for the ASQ will be one month around the first and two months around the second birthday (11 to 13 months and 22 to 26 months respectively).

